**Methods/design:**

This is a population based historical cohort study of all individuals aged 21 years or older (about 2,300,000) who were insured by Clalit Health Services, the largest health maintenance organization in Israel during a ten-year study period. Four study groups will be established according to the status of diabetes and cancer at study entry, Jan 1, 2002: cancer free, diabetes free; cancer free, diabetes prevalent; cancer prevalent, diabetes free; and cancer prevalent, diabetes prevalent. Individuals without diabetes at study entry will be followed for diabetes incidence, and all four groups will be followed for specific cancer incidence, including second primary neoplasms. Glucose control will be assessed by HbA1c and by fasting plasma glucose levels. Time dependent regression models for cancer incidence will account for glucose-lowering medications as they are added and changed over the follow-up period. A large number of demographic and clinical variables will be considered, including: age, gender, BMI, smoking status, concomitant medications, glucose control (assessed by HbA1c and by fasting plasma glucose) and cancer screening tests.

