### Exposure to glucose-lowering medications

In addition to the exposure to diabetes per se, individuals with diabetes will be studied for their exposure to glucose-lowering medications. A drug exposure will be defined as a minimum of 3 purchases of glucose-lowering medications during one year. Each drug exposure will define one type of treatment or a combination of treatments. An individual may be analyzed according to more than one exposure during follow-up time. Drug exposures to be investigated are: each insulin type, meglitinide derivatives, sulfonylureas, biguanides, alpha glucosidase inhibitors, thiazolidinediones, and incretins. An additional group (“no glucose-lowering medication”) will comprise periods of time during which individuals classified with diabetes did not yet purchase glucose-lowering medications.

For each glucose-lowering medication, cumulative exposure will be assessed as the total number of monthly dosages purchased. Daily dosages and daily dosages per body weight will be estimated from records of purchases. Time dependent regression models for the outcomes investigated will account for glucose-lowering medications as they are added and changed over the follow up period, adjusting for constant and time-dependent covariates.

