### Statistical analyses

For our first specific aim, we will compare, after adjustment, all and site-specific cancer rates between individuals with and without diabetes. For the second aim, we will investigate whether metabolic control, as indicated by HbA1c and blood glucose levels, is related to cancer risk. Third, we will evaluate differences in outcomes that associate with the use of one or a combination of glucose-lowering treatments. In all of these analyses we will stratify persons with diabetes by those who were already diagnosed with diabetes at study entry (prevalent diabetes), and those who were diagnosed during follow-up (incident diabetes).

Preliminary data analysis will employ standard methods, starting with calculation of person years and age-gender standardized cancer incidence rates for all sites and selected sites in non-diabetics, and in prevalent and incident diabetics without prevalent cancer. These methods will also be used to investigate potential confounding variables such as baseline smoking status and body mass index. In our analyses of Specific Aims 2 and 3, we will then proceed to use Cox regression with time-dependent treatment variables. For Specific Aim 2, the model will include current and past levels of Hba1c and blood glucose, investigating the level above selected thresholds cumulated over the past n years, where n may be between 1 and 5. For Specific Aim 3 the model will include current and previous treatments. For example, we will investigate exposure to a specific medication when expressed by the cumulative dose or by the cumulative dose over the past 1–5 years. We will investigate exposure to multiple medications, first by models that postulate independent multiplicative effects on cancer incidence rates (no interaction model); and if there are sufficient data, we will proceed to examine interactions between medications on cancer incidence. Due to data limitations, it is unlikely that anything more than pairwise interactions will be able to be examined satisfactorily. The analyses of glucose-lowering medications will take into account the clinical factors (HbA1c, fasting glucose) that may have triggered the change. We will, for example, use the methods of Walker, White, and Babiker

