[21] to better evaluate how HbA1c triggers treatment changes. This may or may not be important for cancer incidence analyses, depending on whether HbA1c and fasting plasma glucose are or are not related to cancer incidence (see Specific Aim 2). In analyses of Specific Aims 2 and 3, we will also be cautious of the possibility of reverse causation, whereby early physiological changes before the diagnosis of cancer may cause deterioration in glucose control and subsequent change in diabetes treatment. We will therefore investigate whether early peaks in cancer incidence rates follow a change in treatment, and will examine model results when all cancer diagnoses are moved backwards in time by a set period of 2 years, 1 year, or 6 months.

As outlined above, in specific analyses, multiple independent sensitivity analyses will be used more generally to test our model assumptions and the robustness of our results. We will look at varying time intervals for the piecewise exponential models, stratification for departures from proportional hazards, interactions and time-dependent models including lagged predictors. Propensity scores will be used as an alternative to direct confounder adjustment, to control for confounding by indication, and to check the robustness of conclusions. We will also explore results obtained by applying the recently described “prior event rate ratio” method of Tannen, Weiner, and Xie
[22], to the analysis of glucose-lowering medications. Though this method will only be applicable to incident cases of diabetes, its effectiveness in controlling for confounding by indication has been reported.

Cancer prevalent cases will be analyzed separately and will have separate adjustments performed, including separate propensity scoring. This is to overcome potential confounding factors associated with cancer treatments and their residual effects. Furthermore, the risk of second primary neoplasms has not been analyzed in diabetes patients, and might have a different pattern of associations with the disease itself and with the use of glucose-lowering therapies than does the risk of first primaries.

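### Aim 3 adjusts cumulative drug exposure for time-updated covariates that earlier treatment can change, so drug hazard ratios can be biased without the stated checks showing it

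*Protocol article*

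**What the plan says.** All places are in the Protocol article.

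- **Model.** Statistical analyses: "In our analyses of Specific Aims 2 and 3, we will then proceed to use Cox regression with time-dependent treatment variables". The end of that section makes PROC PHREG (Cox or piecewise exponential) the primary analysis.
- **Exposure.** Statistical analyses brings in earlier as well as present treatment, for example "exposure to a specific medication when expressed by the cumulative dose or by the cumulative dose over the past 1–5 years".
- **Adjustment.** Exposure to glucose-lowering medications: drugs are modelled "as they are added and changed over the follow up period, adjusting for constant and time-dependent covariates". The time-dependent covariates named at the end of Statistical analyses include cholesterol, concomitant drugs, BMI, blood pressure and comorbidities. HbA1c and fasting glucose are not on that list.
- **Glucose control.** The Abstract counts among the variables considered "glucose control (assessed by HbA1c and by fasting plasma glucose) and cancer screening tests". Statistical analyses adds: "The analyses of glucose-lowering medications will take into account the clinical factors (HbA1c, fasting glucose) that may have triggered the change". It then cites, as an example, a method for evaluating how HbA1c leads to treatment changes, and says its importance depends on whether Aim 2 finds glucose control related to cancer.
- **Checks.** "Propensity scores will be used as an alternative to direct confounder adjustment, to control for confounding by indication". Cancer diagnoses are also shifted earlier by 6 months, 1 year or 2 years, and intervals and lagged predictors are varied. The prior event rate ratio will be explored; the only limit stated is this: "Though this method will only be applicable to incident cases of diabetes, its effectiveness in controlling for confounding by indication has been reported".

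**The concern.** The Background section says that starting and switching treatment may depend on glucose control, and the drugs under study lower glucose. Glucose control is therefore both a cause of the next treatment and a result of the last one. BMI, lipids, blood pressure, other drugs and comorbidities can play the same double role.

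When past treatment is part of the exposure, ordinary regression on the current value of such a covariate does two things. It blocks whatever part of the drug effect passes through the covariate. It also conditions on a common result of treatment and of any unmeasured factor, such as disease severity, and so links treatment to that factor. If the factor also affects cancer, the drug acquires a spurious association. The direction depends on the signs of the paths.

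The aim is to tell apart the cancer effects of individual drugs. A protective drug could be reported as neutral, or a neutral drug as harmful or protective, and an alternative analysis built on the same conditioning could agree with the wrong answer.

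**Working it through.** **1. The plan's own power figure, as a yardstick.** Power calculation states over 80% power for HR 1.4 in two subsets of 6000, two-sided 0.05. Schoenfeld: 4 × (1.960 + 0.842)² / (ln 1.4)² gives 278 events, or 278/12,000 = 2.3%. The cohort average is 175,000/2,300,000 = 7.6%, or about 913 events in 12,000, with power 99.9%. The statement is consistent as a lower bound, and this point does not depend on it. For the 500 to 1000 events that the section mentions, the HR detectable at 80% power with equal groups is exp(2 × 2.802/√events): 1.28 at 500 and 1.19 at 1000.

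**2. Simulation of the adjustment.** Every input here is an assumption; the article gives none.

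- 200,000 persons, 20 half-year steps, 3 replicates per scenario, one drug that is not stopped once started.
- Starting: logit P = −2.6 + 0.9 × HbA1c (centred).
- HbA1c(t) = 0.7 × HbA1c(t−1) − 0.45 × (on drug) + 0.18 × U + noise of SD 0.6. The long-run lowering is 0.45/(1 − 0.7) = 1.5 points. U is an unmeasured standard normal factor.
- Half-yearly cancer hazard: 0.008 × exp(bL × HbA1c + bU × U). The direct drug effect is null throughout.
- Exposure: cumulative years on drug.
- The total effect comes from runs with starting made independent of HbA1c. The weighted model uses stabilised weights, the running product of P(observed start status given time) / P(observed start status given time and HbA1c).

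HR per 5 years of drug:

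| Scenario | Total effect | Conditioned on current HbA1c | Weighted model |
|---|---|---|---|
| HbA1c unrelated to cancer, no shared cause | 0.99 | 1.00 | 0.99 |
| HbA1c HR 1.1 per point | 0.89 | 0.99 | 0.90 |
| HbA1c HR 1.2 per point | 0.80 | 1.00 | 0.80 |
| HbA1c not causal; U has HR 1.3 per SD | 1.00 | 1.27 | 1.01 |
| HbA1c HR 1.2 and U HR 1.3 | 0.80 | 1.26 | 0.79 |

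The SD of the log HR across replicates was at most 0.023. In rows 2 and 3 the conditioned model recovers the direct effect (null), so the gap is one of estimand. In row 4 the conditioned figure is neither the total nor the direct effect. All shifts here are upward because U raises both HbA1c and cancer. If U raised one and lowered the other, the spurious part would point the other way.

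**3. What the stated checks can see.** Shifting diagnoses earlier addresses reverse causation. Varying intervals, interactions and lagged predictors stays within conditional regression. A propensity score that replaces direct adjustment does not solve the problem for cumulative exposure unless it is used as time-varying weights, and the article does not say whether it will be.

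**4. Prior event rate ratio.** The estimate is the post-start rate ratio divided by the pre-start rate ratio. Persons still at risk of a first cancer at drug start have no earlier cancer, so among them the pre-start ratio is 0/0. First cancers can instead be counted in each period. That was simulated with a null drug: 400,000 persons, half intended to start, 3 years before and 5 after, annual hazard 0.0076 (7.6% over ten years), and intended starters at 1.0 or 1.5 times the underlying risk.

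| Share of intended starters with an earlier cancer who still start | Estimate (truth 1.0) |
|---|---|
| 100% | 0.98 to 0.99 |
| 80% | 1.48 to 1.56 |
| 50% | 2.9 to 3.4 |
| 0% | undefined |

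As a hand check with equal underlying risk, the prior ratio is about q(1 − p)/(1 − qp), where p is the starting probability without cancer and q the share who still start. For p = 0.5 and q = 0.8 this is 0.4/0.6 = 0.67, and 1/0.67 = 1.5.

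**The case against.** The article says HbA1c and fasting glucose will be taken into account, not that their current values enter the Cox model, and its covariate list omits them. The cited method for HbA1c-triggered switching cannot be seen here, and the form of the propensity score is left open, so weighting is not excluded. Aim 3 is worded as association, so an effect net of glucose control might be what is wanted. The authors also note that the issue may not matter, depending on Aim 2.

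Much of this stands. Entry of HbA1c is an inference from the Abstract and the two methods sections, though BMI, lipids and blood pressure are named outright. The caveat about Aim 2 helps less than it seems: an HbA1c association produced by a shared unmeasured cause would also appear in Aim 2, and that is the case in which a null drug came out at 1.27.

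A reader might infer several stronger things that the article does not support:

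- **That the drug effects are necessarily biased.** The first scenario shows none.
- **That the prior event rate ratio is the robustness check.** It is exploratory and one of several.
- **That using it for first cancers must give either 0/0 or a mixture with second primaries.** The separate analysis concerns persons with cancer at study entry, so counting first cancers in each period is open. It works if cancer does not alter later drug starting.
- **That a 30% drop in starting after cancer makes a null drug look like 1/0.7 = 1.43.** That holds only when starting is rare. With p = 0.5 the prior ratio is 0.35/0.65 = 0.54, and the result is 1.86.

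**Conclusion.** The concern holds in conditional form. The primary Aim 3 model combines cumulative past treatment with regression on time-updated covariates that treatment can change, and the article names no method for the cancer model that is known to handle this. Drug hazard ratios can then miss the total effect, or be biased in either direction, without the stated checks showing it.

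Under the assumed inputs, a total HR of 0.80 became 1.00 and a null drug became 1.27, shifts about as large as the HRs of 1.19 to 1.28 detectable with 500 to 1000 events. These sizes rest on one simulated drug, a long-run fall of 1.5 HbA1c points, conditioning on HbA1c alone, and treatment starts that depend only on measured HbA1c. The size of the effect through BMI, lipids or blood pressure was not calculated. The bias requires that the covariates affect cancer or share causes with it.

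For first cancers, the prior event rate ratio depends on cancer not changing later drug starting. The article does not state that assumption.

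**What to change.** 1. State whether Aim 3 targets the total effect of a drug or the effect that does not run through glucose control.
2. For the total effect, add an analysis valid for time-varying confounders affected by past treatment, for the main drug classes in incident diabetes. It can use stabilised inverse-probability-of-treatment and censoring weights, or the g-formula, with only baseline covariates in the outcome model.
3. Base total-effect conclusions on that analysis where the weights are stable, and report the conventional time-dependent Cox model alongside.
4. Do not use the prior event rate ratio as evidence that confounding by indication is controlled for first cancers. If it is still explored, state the assumption that cancer does not alter later drug starting.

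No new data are needed. The cost is programming and wider intervals. Weighting may be infeasible for rare drug combinations, so it should not be required for every combination and dose measure. It also relies on measured confounders, and the Potential confounders section says that some, such as smoking, are available only for a subset. Step 4 costs nothing.

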## Methods/design

This is a large scale historical cohort study of all adult individuals insured by Clalit Health Services, the largest health maintenance organization in Israel, insuring and providing healthcare to 55% of the Israeli population (about 3.9 million people). Study entry is defined as January 1, 2002. Inclusion criteria will be: age 21 years or older at study entry and continuous insurance in Clalit Health Services from at least one year prior to study entry, January 1 2001, until the end of the study period, December 31, 2011, or until death, for those who do not survive until the end of follow-up. Of the population of over 2,300,000, over 110,000 had diabetes at study entry; and an additional 350,000 were diagnosed with diabetes during the study period (January 2002 to December 2011).

This study has three Specific Aims: First, we will compare rates of cancer incidence (overall and specific cancers, including second primary neoplasms) in individuals with and without diabetes (separately for prevalent and incident cases of diabetes). Second, we will investigate, in individuals with diabetes, the associations between measures of glucose control, as assessed by HbA1c and fasting plasma glucose, and cancer incidence (overall and specific cancers, including second primary neoplasms). Third, we will compare the incidence of cancer (overall and specific cancers, including second primary neoplasms), among individuals with diabetes who used specific glucose-lowering medications, as well as among patients with no drug exposure (periods of time during which individuals classified with diabetes did not yet purchase glucose-lowering medications, including periods on diet and exercise regimen only).

Four study groups will be established according to the status of diabetes and cancer at study entry, Jan 1, 2002 (Figure
1): cancer free, diabetes free (CF-DF); cancer free, diabetes prevalent (CF-DP); cancer prevalent, diabetes free (CP-DF); and cancer prevalent, diabetes prevalent (CP-DP). Individuals free of diabetes at study entry will be followed for diabetes incidence, and all four groups will be followed for cancer incidence (second primaries for those with prevalent cancer). Nine groups, according to diabetes and cancer prevalence at study entry, and diabetes and cancer and incidence during the study period, will be analyzed (Figure
2).

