The primary analysis will be performed using PROC PHREG of SAS version 9.2, which allows both Cox-proportional hazards models with time-dependent variables and piecewise exponential models. The piecewise exponential model divides time-at-risk into a set of pre-specified intervals with constant baseline hazard in each interval; the use of multiple intervals allows the hazard to vary with time. Clinically important time dependent covariates for the regression models include age, cholesterol (total, LDL, and HDL), concomitant medications (such as statins, beta-blockers, angiotensin converting enzyme inhibitors, and hormone replacement therapy), smoking, body mass index, blood pressure, co-morbidities (such as cardiovascular disease), and reproductive history. For each continuous variable, we will investigate appropriate transformations and interactions that might improve goodness-of-fit. The proportional hazard assumption will be evaluated using log-log survival plots, examination of Schoenfeld residuals, and testing of interactions between variables and time.

While we can not describe, or even anticipate, every contingency for this comprehensive project, we are confident that the very well qualified team has the expertise to evaluate the data.

This study was approved by the ethics committees of Sheba Medical Center, Tel Hashomer and Clalit Health Services, Israel.

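### The reverse-causation check is worded as moving cancer dates only; done literally, it biases hazard ratios downward for drugs whose users have higher mortality and, on some time axes, for drugs first used late

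*Protocol article*

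**What the plan says.** For Aims 2 and 3, the Statistical analyses section recognises that a cancer not yet diagnosed may worsen glucose control and prompt a change of treatment ("we will also be cautious of the possibility of reverse causation"). It plans two responses. One is to look for a rise in cancer incidence soon after a treatment change. The other is to re-examine model results when "all cancer diagnoses are moved backwards in time by a set period of 2 years, 1 year, or 6 months". The sentence names cancer dates as the thing moved and is silent on every other exit from follow-up.

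The end of observation that the article names is in Methods/design, within the inclusion criterion on continuous insurance: "until the end of the study period, December 31, 2011, or until death, for those who do not survive until the end of follow-up". Entry is common to everyone ("Study entry is defined as January 1, 2002").

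For these aims "we will then proceed to use Cox regression with time-dependent treatment variables"; piecewise exponential models are also named. The time axis is not stated. Among general robustness checks the section also lists "interactions and time-dependent models including lagged predictors", with no lag lengths and no link to reverse causation.

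**The concern.** Moving the outcome back by L years is equivalent to lagging exposure by L years only if every exit moves by L. If cancer dates alone move, nobody can have an event in the last L years before death or before 31 December 2011. The diagnosis that would have been moved into that window lies beyond the end of observation, yet the window still counts as time at risk. Groups for whom it is a larger share of follow-up look safer than they are. These are users with higher mortality and, depending on the time axis, users of drugs first taken late in the decade. Aim 2 is exposed in the same way if mortality differs by glucose control.

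At stake is how the check is read. A harmful association that shrinks steadily as the shift goes from 6 months to 2 years is what reverse causation would produce. Here the date arithmetic alone could produce it.

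**Working it through.** **Inputs.** From the article: L = 0.5, 1 and 2 years; entry 1 January 2002; end at 31 December 2011 or death; Cox and piecewise exponential models. Not in the article, so assumed: mortality by drug, cancer rate and drug-start pattern. The plan gives no figure for this check, so there is none to reproduce.

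**Step 1: mortality.** Let λ be the cancer hazard and μ the mortality. A shifted event at time t is a real diagnosis at t + L, so the person must survive to t + L. To be in the risk set at t, the person need only be alive at t. For small λ the apparent hazard is therefore about λ × exp(−μL). For a drug without effect, the ratio of users to comparators is

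HR ≈ exp(−d × L), with d = μ(users) − μ(comparators).

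The time axis does not enter the argument.

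| Assumed mortality per year | d | 6 months | 1 year | 2 years |
|---|---|---|---|---|
| 5% vs 3% | 0.02 | 0.99 | 0.98 | 0.96 |
| 8% vs 2% | 0.06 | 0.97 | 0.94 | 0.89 |
| 10% vs 3% | 0.07 | 0.97 | 0.93 | 0.87 |
| 15% vs 3% | 0.12 | 0.94 | 0.89 | 0.79 |

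To see the effect on a real signal, take the hazard ratio of 1.4 from the Power calculation section and d = 0.06. The shifted results would be about 1.4 × 0.970 = 1.36, 1.4 × 0.942 = 1.32 and 1.4 × 0.887 = 1.24.

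**Step 2: late start.** On time since 1 January 2002, no shifted event falls in the last L calendar years. Those years form no Cox risk sets, so nothing is distorted. On an axis unrelated to calendar time, such as age, the empty years are mixed with informative ones. Suppose a drug is started evenly over the last 5 years and comparators start evenly over all 10, with rare events and negligible mortality. The share of person-time that can hold an event is ((5 − L)/5)² for the drug and ((10 − L)/10)² for comparators:

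- 6 months: 0.81 / 0.9025 = 0.90
- 1 year: 0.64 / 0.81 = 0.79
- 2 years: 0.36 / 0.64 = 0.56

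**Step 3: simulation with no drug effect.** The main run used 1.5 million people with diabetes and time-dependent drug start. Cancer was 1.2% per year, mortality 3% off drug and 3% or 10% on drug, and the late drug was available from year 6. The estimate was a Mantel-Haenszel rate ratio in 2-month strata, which approximates Cox. Only cancer dates were moved.

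| Scenario | 6 months | 1 year | 2 years |
|---|---|---|---|
| Mortality 10% vs 3%, study-time axis | 0.96–0.97 | 0.93–0.94 | 0.89–0.91 |
| Late drug, equal mortality, time since diabetes diagnosis | 0.85 | 0.72 | 0.43 |
| Late drug, 10% vs 3%, time since diabetes diagnosis | 0.83 | 0.67 | 0.40 |

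At 2 years, the late drug with equal mortality on the study-time axis gave 0.97–1.01, the same as after full correction. An ordinary start with equal mortality gave 0.99–1.01 on either axis.

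Further runs covered other axes, with equal mortality and a drug started in the last 5 years against comparators starting over all 10. At 6 months, 1 year and 2 years they gave:

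- age axis: 0.88, 0.79 and 0.54, close to step 2
- time since drug start (cancer 2% per year): 0.85, 0.68 and 0.46
- calendar intervals 5 years wide: 0.91, 0.86 and 0.68
- narrower calendar intervals: 0.94 at 2 years with 2.5-year intervals, and no bias with 1-year intervals

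**Step 4: correction.** In the main run, moving cancer, death and 31 December 2011 by the same lag gave 0.97–1.02 in all scenarios, which is simulation noise around 1. Moving 31 December 2011 but not death left the mortality part in place (about 0.90 at 2 years).

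**The case against.** The strongest reply is that the fixed exits are an inference. The words "until the end of the study period, December 31, 2011, or until death" belong to an insurance eligibility criterion; they are not a censoring rule for the shifted analysis. No sentence says that death and study end stay put, and a fuller analysis plan may move them. That stands, and the point is therefore conditional on a literal reading. It is still more than missing detail, because the article states a concrete rule with its object and three lengths, and that rule is wrong if followed as written.

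A reader might infer that late-started drugs will look protective in general. The article does not support that. The effect is absent in a Cox model on time since 1 January 2002, and the common entry date, with age listed as a covariate, fits that axis. But the axis is not named, and the emphasis in the Discussion on newly diagnosed people and duration of diabetes makes a duration axis plausible. Piecewise models ("The piecewise exponential model divides time-at-risk into a set of pre-specified intervals with constant baseline hazard in each interval") share the problem only when intervals are wide.

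A reader might also infer that a true harmful signal would be dismissed. No decision rule makes this check decisive. The search for early incidence peaks involves no date shift, and the lagged-predictor models do not have the mismatch. Those models are, however, neither tied to reverse causation nor given lag lengths. If they and the date shift disagreed, the article does not say which would be believed.

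Finally, the mortality part is modest, and what counts is the mortality difference left after covariate adjustment. With a 2-point difference the distortion is 1% at 6 months and 4% at 2 years. That stands too.

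**Conclusion.** The point holds in conditional form. If only cancer dates move, a drug whose users have higher mortality has its hazard ratio multiplied by about exp(−d × L) on any time axis. At 2 years the factor runs from 0.96 to 0.79 for assumed differences of 2 to 12 percentage points. Drugs first used late are pulled down further on time since diagnosis, time since drug start or age, or with wide piecewise intervals, and not on study time in a Cox model. All sizes rest on assumed mortality, cancer rates and start patterns, since the article reports none.

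The main estimates are untouched. What is weakened is a secondary check on a bias that the article itself names, because attenuation that grows with the shift could be mistaken for reverse causation. Severity is moderate; the documents do not support treating it as a flaw that must be fixed before the study can proceed.

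**What to change.** Reword the check in one of two ways.

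1. Preferred: lag the exposure and the HbA1c and glucose histories by 6 months, 1 year and 2 years, and leave cancer, death and end-of-study dates unchanged. This ties the lagged-predictor models already planned to the reverse-causation question and gives them lag lengths.
2. If dates are to be moved: move cancer, death and 31 December 2011 back by the same lag for every person.

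In either case, name the time axis of the Cox models.

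The cost is one sentence and a small programming change. Some events and person-time in the first L years are lost.
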